**Fig. 3 Fig3:**
[figure not shown]
Use of PRISM within Project CASCADE

We will use the Primary Care Model (PCM) [41] to guide the evaluation of Project CASCADE. The PCM is empirically derived from a primary care-based preventive services intervention and envisions primary care clinics as complex, adaptive systems (Fig. 4) [41–43]. The PCM complements PRISM by assessing the motivation of clinic stakeholders, resources for change, opportunities clinics have to engage in change, and the effect of clinic’s external environment.

**Fig. 4 Fig4:**
[figure not shown]
Practice change model

PRISM and PCM are both highly pragmatic, highlighting interaction of external and internal determinants to maximize learning from real-world settings.

### Intervention

The intervention will include three evidence-based components: (1) Training to enhance PCC knowledge of cancer survivorship care; (2) Tracking cancer survivors; and (3) Coordinating survivors’ care (Table 2). We used the forms/functions model to inform the development of the intervention [44]. Through this approach, we focus on intervention functions (the purpose of intervention components) and will then develop context-specific intervention forms for implementation to enhance intervention fidelity, adoption, and sustainment [40].

**Table 2 Tab2:** Intervention components, functions, and anticipated forms

Barrier	Component	Expected Form(s)	Target
Lack of knowledge of cancer survivorship and follow-up	**Training** Enhance PCC knowledge of survivorship care	Provider-to-provider tele-mentoring	Clinic leaders and clinic team members
Insufficient attention to past history of cancer during primary care visits Uncertainty in primary care roles and responsibilities Lack of communication between Oncology and Primary Care	**Tracking** - Systematically identify cancer survivors - Monitor care delivery processes	Workflow modification Clinician reminders Survivorship care resources, e.g., Mobile apps recommended by the American Cancer Society	Clinicians and clinic staff
	**Coordinating** Designate a care coordinator champion	Designated personnel: e.g., MA, RN, or social worker to fit CHC context	Clinic staff, oncology partners, and cancer survivors

Training to enhance PCC knowledge of cancer survivorship care will include provider-to-provider tele-mentoring. Tele-mentoring sessions foster problem-solving through live dialogue between cancer experts and CHC teams to integrate survivorship care into routine practice [45–47]. These 1-h collaborative learning sessions will include didactic training and case-based learning using real patient cases identified by CHC teams. Clinic leaders will identify team members to participate in sessions, identify cases for discussion, and determine the schedule for the monthly sessions. Following each session, we will administer a brief survey to assess change in knowledge and attitudes regarding session content.

Tracking will include systematically assessing cancer history and monitoring survivors’ care to plan and organize subsequent care. Trained practice facilitators will work closely with clinic members to assess current workflows, staff roles and responsibilities, and existing chronic disease tracking processes. We will co-create protocols to assess cancer history using quality improvement (QI) tools. The clinic team may also create a cancer survivor registry or explore available EHR tools to aid in identifying and tracking survivors [48].

Coordinating requires each clinic leader to designate at least one staff member to be the care coordinator champion [49, 50]. Coordinator tasks will include gathering records, referring for appropriate screening, following up on results [39], and assisting patients in self-management [49, 51, 52]. Clinic leaders will determine task responsibilities, requisite competencies and supplemental training needs, practical frequency of contact, and how to monitor or measure performance. The clinic team will co-design, with practice facilitator support, survivorship resources at point of care, workflows operationalizing coordination pathways, and supporting patient outreach, awareness, and education. Monitoring may occur by telephone consultation or during in-person visits, either supplemental or adjacent to routine PCP visits [53–55].

### Implementation strategies

Two strategies (partner engagement and practice facilitation) will support intervention. Our evaluation will identify other emergent strategies and delineate mechanisms of implementation (Aim 3).

#### Partner engagement

FQHC Board of Directors composition must be 51% patients and include community members reflecting demographics of the service area [56–58]. Upon each clinic’s enrollment, clinic leaders will work with us to convene representatives of their Board, including at least one patient/client, and clinic staff designated by leaders (e.g., clinic manager). We will use group participatory approaches [59–61], drawing on participatory research principles [62–65], to engage partners in discussing challenges to delivering survivorship care in their specific setting. These techniques elicit cross-cutting perspectives grounded in the lived experience of each partner, generate insights from the local context, foster buy-in and accelerate group cohesion [66]. Eliciting these insights help establish shared goals of shaping clinic workflows to local context, thereby, increasing likelihood of the clinic’s ability to change [42]. The retreat will have three sessions: The Mission and Vision: Summarize latest evidence on cancer survivorship, present an environmental scan of oncology practices in CHC community (generated collaboratively by clinic teams and investigators) and brainstorm ways to partner with oncology representatives, and generate discussion about value of strong primary care-oncology partnerships; The Journey: Invite oncology and primary care partners to explore objectives for and challenges to care coordination focusing on concepts of shared leadership, [67–70] defined roles and responsibilities [71], then to brainstorm workflow changes that facilitate care for cancer survivors [72]; and The Tools: Present intervention functions and explore clinic-specific implementation of intervention forms, i.e., survivor identification and monitoring, the coordination role, and clinic workflow adaptation. Our clinic leaders are motivated to “dive in” for this collaborative approach to survivorship care. After each session, to stimulate discussion and solicit opinions to guide course correction, we will field a short, five-minute pragmatic survey modeled on existing measures, [73–75] to monitor acceptability, appropriateness, and feasibility, as real-time audit and feedback. Following the retreat, we will convene each clinic group quarterly to provide updates, maintain momentum, and resolve emergent challenges to ensure continued engagement of partners throughout implementation. Flowing from the retreat, we will meet with clinic teams over a three-month period to map components [76] to adapt workflows [77] to tailor implementation.

#### Practice facilitation

We will support each clinic’s intervention implementation by providing facilitation in quality improvement (QI) by a trained facilitator [78]. Facilitators will employ strategies to promote QI activities while also building capacity, [79] while strengthening our relationship with each CHC and team. Strategies include building relationships within teams, providing value by contributing EHR expertise, and remaining flexible throughout the QI change effort [80]. Facilitators will determine each clinic team’s readiness for change using the Organizational Readiness for Change measure [81] and will identify current needs and “pain points” [82]. While we have clinic leadership buy-in, it is critical to also cultivate buy-in from team members on the ground to promote intervention adoption. The facilitator will work with clinic teams in designing intervention forms that will achieve the tracking and coordinating functions. For example, the facilitator will support the designated care coordinator in planning and testing the process of assessing and monitoring survivors’ survivorship care needs. They will utilize established techniques such as PDSA cycles [83], clarifying roles and identifying champions [50], building trust through experience-based problem solving [84], workflow modification via cognitive walk-throughs [85, 86].

### Intervention rollout

The intervention will be implemented in each clinic over 12 months. Tele-mentoring sessions will start after the partners’ retreat for two clinics randomized to each block of the stepped-wedge design (Fig. 2). Tracking and coordinating components will “go live” during the week following the first tele-mentoring session. Modified workflows will assess patients for a history of cancer, at or before routine visits (e.g., through patient portal or via phone call). Each week, the “care coordinator” will review records for indication of cancer history, document cancer history in the problem list using a standardized format developed by the team, request records from oncology providers as needed, and pend to patient record with notification to PCC. We expect that PCCs will apply survivorship care knowledge gleaned from tele-mentoring sessions to plan survivors’ ongoing care. For patients who have finished cancer treatment, the coordinator will review treatment summary and care plan upon receipt and assess survivorship care needs (e.g., screening for second primary cancer, adherence to recommended cancer surveillance). For patients in active cancer treatment, the coordinator will facilitate communication [87] with oncology about appointments, treatments, and potential impact on chronic disease care, and encourage continued connection with primary care [88–90]. The coordinator will review with each patient roles and responsibilities of respective providers, advise on appropriate follow-up, and encourage continual interaction with their primary care team. They will also ensure patients receive relevant referrals to smoking cessation, diet and exercise, and psychosocial counseling, as appropriate. Information and education will be culturally and literacy-level appropriate. Practice facilitators will set up monthly in-person or web meetings to help the clinic team reflect [86] and discuss how to identify survivors, clarify team member roles, foster communication, manage care transitions, and monitor or adjust workflow [91–94].

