### Randomization procedures

We will randomize 8 CHC clinics in blocks of two every six months in a stepped-wedge design (Fig. 2). Each clinic team will implement the intervention over a 12-month period. The time before the intervention will serve as the usual care (control) condition, while the period during and after the intervention will constitute the treatment condition.

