### Outcomes

The primary outcome for this study is the proportion of patients who have received guideline-concordant screening to detect second primary cancers (i.e., breast, cervical, colorectal, lung, and prostate cancer screening for which there are established clinical NCCN guidelines). This outcome is an NCCN guideline [95], is clinically significant, and relevant for CHCs [96]. Cancer survivors have higher risk for second cancers, so increasing screening aids early detection and treatment, reducing morbidity and mortality [95, 97]. Moreover, this outcome is pragmatic, falling within the scope of primary care practice and pertinent to CHCs annual Uniform Data System (UDS) performance metrics [98]. We hypothesize that compared to usual care periods, post-intervention periods will have higher rates of cancer screening for second primary cancers among cancer survivors seen during routine primary care.

We will assess the following secondary outcomes:Physician-reported cancer survivorship care knowledge and skills. We hypothesize that in the post-intervention periods, physicians will report enhanced cancer survivorship care knowledge and skills compared to the usual care period. Provider knowledge and skills will be assessed by self-administered survey.Experience of cancer survivors with care coordination. We hypothesize that patients will report better experience with care coordination post-intervention compared to usual care. Patients' experience with care coordination will be assessed via survey.Adherence to NCCN surveillance guidelines for breast, cervical, colorectal, lung and prostate cancer. We hypothesize that post-intervention periods will have higher rates of guideline-concordant cancer surveillance compared to usual care periods [99–103].

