### Quantitative data collection

#### EHR extraction/audit

The study team with support from clinic EHR specialists will extract EHR data for eligible patients at the end of every 6-month period. Extracts will include all patients with a history of cancer who were seen in the respective 6-month period.

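### Filing outside records is part of the intervention and the outcome appears to be read from the clinic EHR, so capture of outside screening could improve at crossover and be counted as effect

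*Protocol article*

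**What the plan says.** The Outcomes section defines the primary outcome as "the proportion of patients who have received guideline-concordant screening to detect second primary cancers". This is a status, so a test done outside the clinic counts if it is known.

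The EHR extraction/audit section says that the study team "will extract EHR data for eligible patients at the end of every 6-month period" and that "Extracts will include all patients with a history of cancer who were seen in the respective 6-month period". The abstract lists EHR, survey, interview and observation data. No other patient-level clinical source, such as claims or a registry, is described.

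The Intervention section states: "Coordinator tasks will include gathering records, referring for appropriate screening, following up on results". The Intervention rollout section adds that the coordinator will "request records from oncology providers as needed, and pend to patient record with notification to PCC". On timing, the same section says: "Tracking and coordinating components will “go live” during the week following the first tele-mentoring session". Under Randomization procedures, "The time before the intervention will serve as the usual care (control) condition". No matching retrieval of records is described for usual-care periods.

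The Data analysis section fits a clinic random effect, fixed period effects and an intervention indicator. The limitations acknowledge misclassification of cancer history. They do not mention screening status, and the remedy they offer is redesign of clinic workflow, which is itself part of the intervention.

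**The concern.** The intervention is meant to produce more screening. It also changes the record from which screening appears to be measured. If a colonoscopy or mammogram done elsewhere is more likely to be on file after crossover than before, the observed proportion rises without any additional test.

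The model cannot separate the two. Fixed period effects remove trends common to all clinics in a calendar period. A documentation gain that begins at each clinic's own crossover coincides with the intervention indicator and is estimated as part of its coefficient. A positive primary result would then leave open whether more survivors were screened or more past screening was found.

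**Working it through.** **1. The chain in the text.** The outcome is a received-screening status (Outcomes). The only clinical source described is the EHR extract at each period's end (EHR extraction/audit). Record gathering adds to that EHR (Intervention, Intervention rollout). It begins after crossover, and earlier time is control (Intervention rollout, Randomization procedures). That the primary outcome comes from the EHR is inferred from the abstract and the extraction section together; no single sentence says so.

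**2. The plan's own figures.** Take 8 clinics, 6 periods and 100 patients per clinic-period, with two clinics crossing at each of periods 2 to 5. Treated periods per clinic are 5, 5, 4, 4, 3, 3, 2, 2, which sum to 28. Control clinic-periods are 48 − 28 = 20. This gives 2000 + 2800 = 4800, as stated under Power calculation. The count uses all 48 clinic-periods, although that section says the implementation period is excluded.

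**3. Standard error from the Hussey and Hughes formula.**

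var = I·s²(s² + T·τ²) / [(I·U − W)·s² + (U² + I·T·U − T·W − I·V)·τ²]

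- I = 8, T = 6, U = 28.
- W (sum over periods of squared treated-clinic counts) = 0 + 4 + 16 + 36 + 64 + 64 = 184.
- V (sum over clinics of squared treated-period counts) = 2 × (25 + 16 + 9 + 4) = 108.
- At an assumed 50% rate, individual variance is 0.25. With ICC 0.05 (the plan assumes below 0.05), τ² = 0.05 × 0.25 = 0.0125 and s² = 0.95 × 0.25 / 100 = 0.002375.
- Numerator: 8 × 0.002375 × (0.002375 + 0.075) = 0.001470.
- Denominator: 40 × 0.002375 + 160 × 0.0125 = 2.095.
- SE = √(0.001470 / 2.095) = 0.0265.

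**4. What a documentary gain would do.** Let p be the true screened proportion, unchanged by the intervention, and s0 and s1 the shares of completed tests visible in the EHR before and after crossover. The apparent difference is d = p(s1 − s0). The rejection rate is Φ(d/SE − 1.96) + Φ(−d/SE − 1.96). The documents give none of p, s0 or s1, so the gains below are assumptions.

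| Documentary gain d | Example at p = 0.50 | Rejection at SE 0.0265 | Rejection at SE 0.0375 |
|---|---|---|---|
| 0.010 | 0.88 to 0.90 | 7% | 6% |
| 0.025 | 0.90 to 0.95 | 16% | 10% |
| 0.050 | 0.80 to 0.90 | 47% | 27% |

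The last column assumes a clinic-by-period random effect (cluster autocorrelation 0.8), close in spirit to the alternative model the protocol mentions. Leaving out the first period after crossover in each clinic gives a similar SE, 0.0368, and 27% for a 5-point gain. Over p = 0.40 to 0.60, a 10-point gain in completeness gives d = 0.04 to 0.06. Under the planned model, with the SE recalculated at each observed rate, rejection is then 36% to 62%.

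**The case against.** The strongest reply is that the documents never say that outside tests are missing before crossover. The Outcomes section chose screening partly because it falls within primary care and bears on the clinics' annual performance metrics, so these clinics already have reason to record it. The requests go to oncology providers, only when needed, and the documents named as received are the treatment summary and care plan. Nothing says these contain screening results for a different cancer. Look-back windows and dating rules may also sit in a fuller document. All of this stands, and it limits the claim to a possibility of unknown size.

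Three stronger readings are tempting, and the documents support none of them.

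- **Outside tests are unseen under usual care.** Retrieval in usual-care periods is not described, but silence does not make it zero.
- **Documentation could account for the whole planned 15-point difference.** That follows only from freely chosen inputs. A small recovery rate gives about one point.
- **The period-end cut-off on late-ordered tests favours the intervention.** The cut-off applies in both conditions. If the intervention raises ordering, it could work against the intervention.

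The net direction is also open. More systematic recording of cancer history adds newly identified survivors to the denominator, which could add to the documentation effect or offset it.

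What the reply does not remove is the link in time between record gathering and the intervention indicator. The Intervention rollout section also names second-primary screening among the needs to be assessed when oncology documents arrive, so those records do bear on the outcome.

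**Conclusion.** The point holds as a risk. As written, the plan lets capture of screening done elsewhere improve at crossover, and the primary model would credit that improvement to the intervention. The size cannot be derived from the documents. Under the assumptions shown, a 1-point gain is nearly harmless (about 7% rejection against a nominal 5%), while a 5-point gain would produce a significant result in roughly a quarter to a half of trials with no true effect, depending on the correlation model. The conclusion rests on the primary outcome being EHR-derived and on record gathering being less complete before crossover. The first is a close inference from the text; the second is plausible but not stated. The change is worth making because it costs little and bears on how a positive result would be read.

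**What to change.** - **Key sensitivity analysis.** Pre-specify an analysis of the primary outcome that counts, in both conditions, only tests ordered or resulted through the clinic's own system. Classify every test by date of service and by source (clinic or outside record).
- **Supporting analysis.** Use one final extraction to re-derive every period's status by date of service, so that outside tests recovered later are credited to the usual-care period in which they were valid.
- **Limitations.** Extend the misclassification paragraph to screening status, and say that workflow redesign cannot remedy it evenly because it reaches only periods after crossover.

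The cost is one more EHR pull and a source-and-date field for each test. The clinic-only analysis misses genuine outside screening, including tests that the intervention prompted. The re-derivation misses patients who do not return after crossover and gives early-crossing clinics longer to recover records, so it should support the clinic-only analysis and not replace it. Neither change affects the intervention or the randomization.

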### Outcomes

The primary outcome for this study is the proportion of patients who have received guideline-concordant screening to detect second primary cancers (i.e., breast, cervical, colorectal, lung, and prostate cancer screening for which there are established clinical NCCN guidelines). This outcome is an NCCN guideline [95], is clinically significant, and relevant for CHCs [96]. Cancer survivors have higher risk for second cancers, so increasing screening aids early detection and treatment, reducing morbidity and mortality [95, 97]. Moreover, this outcome is pragmatic, falling within the scope of primary care practice and pertinent to CHCs annual Uniform Data System (UDS) performance metrics [98]. We hypothesize that compared to usual care periods, post-intervention periods will have higher rates of cancer screening for second primary cancers among cancer survivors seen during routine primary care.

We will assess the following secondary outcomes:Physician-reported cancer survivorship care knowledge and skills. We hypothesize that in the post-intervention periods, physicians will report enhanced cancer survivorship care knowledge and skills compared to the usual care period. Provider knowledge and skills will be assessed by self-administered survey.Experience of cancer survivors with care coordination. We hypothesize that patients will report better experience with care coordination post-intervention compared to usual care. Patients' experience with care coordination will be assessed via survey.Adherence to NCCN surveillance guidelines for breast, cervical, colorectal, lung and prostate cancer. We hypothesize that post-intervention periods will have higher rates of guideline-concordant cancer surveillance compared to usual care periods [99–103].

### Quantitative data collection

#### EHR extraction/audit

The study team with support from clinic EHR specialists will extract EHR data for eligible patients at the end of every 6-month period. Extracts will include all patients with a history of cancer who were seen in the respective 6-month period.

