However, there are barriers to leveraging this capacity [20]. Primary care clinicians (PCCs) often do not feel equipped to care for survivor needs [21], lack knowledge about survivorship care guidelines [22–25], and need more experience recognizing and managing the adverse effects of cancer treatments [26]. In addition, there is a perception that cancer prevalence is low in primary care panels [27]. A study of 431 community health centers (CHCs) noted that 3% of adult patients had cancer documented in their electronic health record (EHR) [28]; this is likely an underestimate [28] because of inconsistent documentation. Our chart audit study in two CHC clinics identified 6.5% patients with ≥ 2 chronic conditions had cancer [29].

To address these gaps, *Community and Academic Synergy for Cancer Survivorship Care Delivery Enhancement* (Project CASCADE), a pragmatic, type 2 hybrid implementation-effectiveness trial in Texas-based primary care community health center (CHC) clinics, aims to:Implement a system-level cancer survivorship care delivery intervention in partnership with CHC clinicians, patients, and community representativesTest effectiveness of the intervention to improve patient and clinician outcomes using a stepped- wedge cluster-randomized trial designEvaluate implementation of the intervention using an iterative, concurrent mixed-methods approach guided by the Practice Change Model (PCM)

Accomplishing these aims will enhance the capacity of safety-net primary care teams to manage cancer survivorship in primary care, enabling survivors to receive coordinated, whole-person care.

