### Participants

This system-level intervention will target clinic and clinic teams; patients will receive the intervention passively as part of the care they receive from their primary care teams. Eligible clinic team members include all employed clinicians (MD, DO, PA, NP) and clinic staff (e.g., social worker, medical assistant, care coordinator) of the participating CHC clinics. Eligible patients include current CHC patients that are at least 18 years old with a history of any type of cancer. This is an important pragmatic feature due to the strength of generalist primary care in prioritizing and delivering care for all conditions. An intervention focused on a single cancer is unlikely to be fully integrated into usual practice in community settings [27].

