### Strengths and limitations

This study presents several strengths that make it both innovative and impactful. By working directly with CHCs, Project CASCADE will advance health equity and address care disparities in underserved populations. The participatory and pragmatic approach not only enhances the relevance and responsiveness of the intervention but also increases its likelihood of adoption and long-term sustainability within CHCs. Additionally, the study evaluates the impact of the intervention at multiple levels—clinician, patient, and system — allowing for a comprehensive understanding of both effectiveness and implementation.

The study also has limitations worth noting. Engaging clinics in research can be challenging; however, in our experience, clinics and stakeholders remain more engaged when researchers seek and incorporate their input from the outset. Additionally, implementing practice changes can be burdensome in busy practices; However, this pragmatic intervention was designed to fit closely with scope of primary care practice. Finally, accurate identification of patients with a history of cancer is challenging, raising the risk of misclassification bias. Inconsistent documentation practices or missing historical data within EHRs may lead to underestimation or misidentification of eligible patients but plans for clinic workflow redesign with CHC partners targets these historical inconsistencies.

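### The tracking component can change who is identified as a cancer survivor after go-live, and the stated denominator rule does not protect the primary comparison from this

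*Protocol article*

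**What the plan says.** Under Participants, the protocol states: "Eligible patients include current CHC patients that are at least 18 years old with a history of any type of cancer". No date or source for that history is given. Under EHR extraction/audit, the study team, with clinic EHR specialists, "will extract EHR data for eligible patients at the end of every 6-month period", and "Extracts will include all patients with a history of cancer who were seen in the respective 6-month period". The Power calculation section also drops survivors who screened positive in an earlier period, but nothing there restricts how or when cancer history must have been recorded.

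The intervention acts on that same record. Under Intervention rollout, once a clinic goes live, "Modified workflows will assess patients for a history of cancer, at or before routine visits". Each week the care coordinator is to "review records for indication of cancer history, document cancer history in the problem list using a standardized format developed by the team". The Intervention section adds that a clinic may build a survivor registry.

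The protocol accepts that recording is incomplete. The Introduction gives 3% of adults with documented cancer in a study of 431 health centers and comments that "this is likely an underestimate". It then reports 6.5% from the team's own chart audit. Strengths and limitations names misclassification as a risk and answers that "plans for clinic workflow redesign with CHC partners targets these historical inconsistencies".

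**The concern.** The treatment modifies the field that decides who is counted. Before crossover, a survivor enters the denominator through whatever documentation usual care has produced. After crossover, the denominator can also contain survivors found because the clinic asked, searched and recorded. If these additional patients have a different screening rate, the proportion screened moves with no change in anyone's care.

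The remedy offered in Strengths and limitations does not help the comparison. The redesign improves ascertainment only in clinics that have crossed over, so it can turn misclassification that was similar in both conditions into misclassification that differs by condition.

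The planned analysis does not absorb this. Under Data analysis the model has a clinic random effect, fixed period effects and an intervention indicator. Clinics cross over at different times, so a shift that starts at crossover is neither constant within a clinic nor common to a calendar period; it loads on the intervention indicator. The covariate rule brings in only baseline variables found to be unbalanced. At stake is whether the estimated effect reflects more screening or a different set of patients.

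**Working it through.** **Inputs from the protocol.** Eight clinics, two crossing over every six months (Randomization procedures). Six periods with 100 patients per clinic-period, about 2000 under usual care and 2800 under intervention; ICC below 0.05, taken here as 0.05; two-sided alpha 0.05; target difference 0.15 with at least 85% power (Power calculation).

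**Assumptions.** The first crossover follows one all-control period, which is the layout that reproduces the stated split. The total variance is 0.25, since no base rate is given. The documents give neither f nor g, so both are assumed.

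**Step 1: the plan's own figures.** With crossovers after periods 1, 2, 3 and 4, control clinic-periods number 2 × (1 + 2 + 3 + 4) = 20 and intervention clinic-periods 2 × (5 + 4 + 3 + 2) = 28. At 100 each this is 2000 + 2800 = 4800, as stated.

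**Step 2: standard error.** The Hussey and Hughes variance is

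I·s²·(s² + T·τ²) / [(I·U − W)·s² + (U² + I·T·U − T·W − I·V)·τ²]

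with I = 8, T = 6, s² = 0.95 × 0.25 / 100 = 0.002375 and τ² = 0.05 × 0.25 = 0.0125. Here U = 28 is the number of intervention clinic-periods. W = 0 + 4 + 16 + 36 + 64 + 64 = 184 sums the squared period totals, and V = 2 × (25 + 16 + 9 + 4) = 108 sums the squared clinic totals.

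- Numerator: 8 × 0.002375 × 0.077375 = 0.001470.
- Denominator: 40 × 0.002375 + 160 × 0.0125 = 2.095.
- Variance 0.000702, so SE = 0.0265.

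Power for 0.15 exceeds 99.9%, so the stated lower bound of 85% is met on these inputs. The smallest estimate that reaches p < 0.05 is 1.96 × 0.0265 = 0.052.

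**Step 3: shift with no true effect.** Let p be the screening rate in survivors whom usual care would identify. In intervention periods the expected proportion is (1 − f)·p + f·(p + g) = p + f·g, so the spurious effect is f × g.

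| f | \|g\| = 0.10 | \|g\| = 0.20 | \|g\| = 0.30 |
|---|---|---|---|
| 0.10 | 1.0 points | 2.0 points | 3.0 points |
| 0.25 | 2.5 points | 5.0 points | 7.5 points |
| 0.37 | 3.7 points | 7.4 points | 11.1 points |

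At |g| = 0.20 the chance of a two-sided rejection with no true effect is about 12%, 47% and 80% for the three values of f, against a nominal 5%. A simulation of the same model (2000 runs) gave a mean estimate of 0.050 and 46% rejection at f = 0.25, g = 0.20. With f = 0 it gave 0.001 and 5.1%.

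The value 0.37 is illustrative. It is what results if recorded prevalence rises half of the way from 3% to 6.5%: 1.75 / (3 + 1.75) = 0.37.

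**Step 4: gradual build-up.** The fitted effect weights a shift by time since crossover. From the first to the fifth intervention period the weights in this layout are 0.886, 0.443, 0.005, −0.191 and −0.143 (sum 1). Take f = 0.15, then 0.26, then 0.37 throughout, with g = 0.20. The spurious effect is 0.20 × [0.15 × 0.886 + 0.26 × 0.443 + 0.37 × (0.005 − 0.191 − 0.143)] = 0.20 × 0.126 = 0.025, or 2.5 points. Reaching 0.37 already in the second intervention period gives 3.5 points; a linear rise over all five gives 2.2. All are well below the 7.4 points for f = 0.37 from crossover.

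**Step 5: the other sign.** With g negative, a real effect is diluted. For f = 0.37 and g = −0.20 from crossover, a true 0.15 has an expected estimate of 0.15 − 0.074 = 0.076 and power of about 82%.

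**The case against.** The strongest reply is that the protocol never says usual-care extracts contain only survivors on the problem list. The section heading includes the word audit, the team has identified survivors by chart audit before, and the coordinator works partly from histories already in the record. An extraction that searched beyond the problem list would find some of those patients before crossover too. The case-finding algorithm is also detail that an article may leave to the full protocol. This stands as far as it goes: a reader might infer that every newly recorded survivor is invisible under usual care, and the text does not support that. The concern does not need it. Asking patients directly creates information that no earlier extract could hold, and the rule as stated sets no barrier between intervention documentation and the denominator.

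A reader might also set 3% against 6.5% and conclude that up to 54% of survivors are undocumented (1 − 3/6.5), giving a shift of 10.8 points at a 20-point difference. The documents do not support this. The 3% refers to all adults in 431 centers, the 6.5% to patients with at least two chronic conditions in two clinics. Patients with several conditions may simply have more cancer, so the ratio neither measures nor bounds the undocumented share. The 20-point difference is likewise an assumption.

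The reply that tracking works through visits and weekly review over 12 months is also correct, and step 4 shows that it matters. Finally, the protocol does disclose misclassification, but as a general limitation; it does not recognise that misclassification may differ by condition.

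**Conclusion.** The concern holds as a matter of mechanism: the stated denominator rule lets the intervention influence who is counted, and the planned model cannot separate that from a change in screening. Confidence is high for the mechanism and low for its size. The sign is unknown, because newly found survivors could be screened less or more often than those already documented.

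Under assumed values the spurious effect ranges from negligible (1 point at f = 0.10, |g| = 0.10) to about half the planned 15 points (7.4 at f = 0.37, |g| = 0.20 from crossover). Gradual accrual brings the latter down to between 2 and 4 points. The significance threshold of about 5 points rests on ICC 0.05, variance 0.25 and 100 patients per clinic-period. More patients would not help: they shrink the standard error and leave the bias in place.

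**What to change.** Keep the open cross-sectional design. For the primary analysis, define survivor status by one fixed ascertainment rule, applied identically to all clinics and periods and using only sources that intervention documentation cannot alter. Two workable forms:

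- a fixed code list that excludes entries created by the tracking workflow, which requires those entries to be flagged when they are made; or
- one retrospective ascertainment applied equally to control-period and intervention-period visits. It must not lean on tracking entries, because a control-period patient who never returned after go-live had no chance of receiving one.

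Add a sensitivity analysis limited to survivors documented before the first crossover. Report the number newly identified per clinic-period as an implementation outcome, so that f can be seen. Reword Strengths and limitations to say that the redesign may make misclassification differ by condition.

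Using the survivors documented before one common date as the primary population would also remove the bias. It would, however, turn the open design into a shrinking closed cohort and change the question asked, so it is better kept as the sensitivity analysis.

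The cost is extraction wording, a flag on tracking entries and slightly more extraction work. Some newly found survivors leave the primary analysis, so some cells become smaller. The rule should be fixed before the control-period extracts are finalised.
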